## Abstract

**Background:**

There is a need to improve psychotherapeutic approaches to treatment for vulnerable older adults with depression in terms of both clinical practice and health care supply. Against this background, PSY-CARE is testing the feasibility and effectiveness of outpatient psychotherapy for home-living older adults in need of care with depression in Berlin, Germany, and neighboring suburban areas.

**Methods:**

In a two-arm single-center pragmatic randomized controlled trial (RCT), manual-guided outpatient psychotherapy will be compared to brief psychosocial counseling. The study population will be compromised of older adults with clinically significant depressive symptoms who have a long-term care grade, as assessed by the German compulsory state nursing care insurance. In the intervention group, individual cognitive-behavioral psychotherapy tailored to the specific needs of this population will be offered by residential psychotherapists as part of the regular healthcare service. In the active control group, participants will receive individual psychosocial telephone counselling and a self-help guide. The planned sample size is *N* = 130 (*n* = 65 participants per group). The reduction of depressive symptoms (primary outcome) as well as the maintaining of activities of daily living, quality of life, and functioning will be assessed with questionnaires provided at baseline, after the end of the intervention and after three months. Feasibility and process evaluation will be conducted qualitatively based on documentation and interviews with psychotherapists, gatekeepers and the participants.

**Discussion:**

PSY-CARE investigates the potentials and limitations of providing outpatient psychotherapeutic treatment meeting the demands of vulnerable home-living older adults with depression under the real conditions of the health care system. The study will provide practical implications to improve access to and quality of outpatient psychotherapy for this poorly supplied population.

**Trial registration:**

The trial is registered at ISRCTN55646265; February 15, 2019.

**Supplementary information:**

**Supplementary information** accompanies this paper at 10.1186/s12877-020-01661-1.

## Background

Depression is a common phenomenon among vulnerable older adults. Compared with the general older population, community-based studies have consistently documented at least two or three times higher rates of depression among older adults with chronic physical conditions, cognitive deficits and/ or sensory limitations, i.e. conditions that often along with functional impairment and dependence on informal and formal support systems for medical care, transport and other essential needs (e.g., [1–5]). Conversely, depression has devastating consequences for older individuals including an increased risk of morbidity and suicide, decreased physical, cognitive and social functioning, all of which are in turn associated with higher rates of service utilization, premature institutionalization and mortality [6, 7].

Meta-analyses and systematic reviews have provided extensive evidence that psychotherapeutic interventions are effective for treating depression in the older population, with strongest evidence for cognitive and behavioral therapy (CBT), life review therapy (LR) and problem-solving therapy (PST) [8, 9]. However, vulnerable older adults with depression including very old, frail and care-dependent older adults were mostly excluded from these studies [10], despite advances for psychotherapeutic research in the context of specific comorbid conditions including chronic obstructive pulmonary disease (COPD), heart failure, Parkinson’s disease, stroke, early stages of dementia and suicidal ideations [for an overview, see [11]]. As a result, psychotherapy for this rapidly growing population is understudied in terms of clinical practice, feasibility, efficiency and effectiveness.

The described deficiencies in research are also mirrored in the massive shortage of mental health care supply for vulnerable older adults with depression [e.g., [12]]. Under the current conditions of health care systems, referrals to outpatient psychotherapy very seldom succeed due to health care providers’ pessimistic attitudes towards vulnerable older patients’ treatability, patients’ inaccessibility, shortage of psychotherapists qualified to work with older adults, and costs (e.g., [13–15]). For example, although outpatient psychotherapy is integral part of public and private health care in Germany, ambulatory psychotherapy is de facto non-existing or only in very exceptional cases among vulnerable older people in need of care [16]. The fact that vulnerable older adults’ mental health care needs are obviously largely unmet is even more problematic as most of them have positive attitudes towards psychotherapy or even prefer psychotherapy to pharmacotherapy, contrary to what is often believed [17, 18].

The significant correlation between depression and impaired quality of life together with increasing numbers of vulnerable older adults and the very poor supply reality highlight the importance of developing and rigorously evaluating appropriate psychotherapeutic approaches, including outpatient psychotherapy for home-living vulnerable older adults.

When it comes to clinical practice, existing studies on mental health services for homebound older adults and nursing-home participants has clearly shown the necessity of gatekeepers (such as aging services networks for patients to gain access to mental health care providers), interprofessional collaboration, caregiver involvement and in-home treatment (for patients who cannot freely leave their home [19, 20]). Furthermore, vulnerable older patients have been shown to profit from CBT and PST through encouragement of adaptive coping skills together with behavioral activation and increased exposure to pleasant events (e.g., [21–23]). Finally, research on LR in long-term care has shown the importance of reminiscence and biographical interventions for patients in order to identify coping skills in their biography as well as to find hope and purpose in life (e.g., [23, 24]).

### Objectives

PSY-CARE investigates the feasibility and effectiveness of individual outpatient psychotherapy within the regular German health care system for home-living older adults in need of care with clinically significant depression. Outpatient psychotherapy tailored to the specific needs of this population is provided based on a treatment manual by certified resident CBT psychotherapists with extensive professional experience in geriatric or geropsychiatric settings.

In terms of the effectiveness of the intervention, we hypothesized that psychotherapy leads to a greater reduction of depressive symptoms, which we considered the primary outcome, compared to an alternative intervention, which encompassed brief psychosocial counselling (Hypothesis 1). Further, we hypothesized that psychotherapy will be associated with a relative difference at follow-up in the secondary outcomes – i.e., quality of life, activities of daily living, functioning and subjective health – in the intervention condition compared with the control condition (Hypothesis 2). More specifically, we assume maintenance of activities of daily living and quality of life, and functioning/ subjective health in the intervention condition relative to the control condition, which we assume shows a decline. Further, in this trial treatment response (50% or greater reduction in depressive symptoms from baseline to follow up) and remission [defined as number of individuals who scoring below the cut-off of 10 points at the Geriatric Depression Scale (GDS; [25, 26] at follow up] will be used as secondary outcomes.

In terms of the feasibility of the intervention under the real conditions of the German health care system, a wide range of approaches to recruit participants of this hard-to-reach population is used and effective versus non-effective recruitment methods are documented. In addition, we aim to explore possibilities and constraints of psychotherapists’ clinical practice of working with home-living vulnerable older adults including their professional experiences with home treatment in case of participants’ limited mobility, as well as collaboration with other healthcare professionals, especially with general practitioners and formal or informal caregivers.

## Methods/design

### Trial design

PSY-CARE is a single-center interventional study, using a pragmatic randomized controlled design with nested qualitative research, comparing individual psychotherapy with an active control condition. The intervention condition will include manual-guided psychotherapy provided by gerontologically trained resident psychotherapists [27]. The active control condition will include individual telephone counselling carried out by project staff members as well as a self-help guide for participants and their caregivers [28]. The flow chart of the study design is depicted in Fig. 1. The schedule of enrolment, interventions, and assessments is shown in Table 1.

**Fig. 1 Fig1:**
[figure not shown]
Flow chart of participants of the PSY-CARE trial

**Table 1 Tab1:**
[figure not shown]
Schedule of enrolment, interventions, and assessments of the PSY-CARE trial

^a^ Three probationary sessions and up to 24 therapy sessions

^b^ Individual telephone counselling, which is offered two times per participant and per caregiver carried out by trained staff members as well as self-help literature for participants and their caregivers

*GDS* Geriatric Depression Scale, *WHOQOL-OLD* single item of the World Health Organization Quality of Life in OLD age. *Mini-DIPS* German structured clinical interview for the diagnose of depressive symptoms. *HADS* Hospital Anxiety and Depression Scale. *BI* Barthel-Index (Activities of daily living). *IADL* Instrumental Activities of Daily Living-Scale at. *T1* Time point 1, baseline. *T2* Time point 2, after the intervention

PSY-CARE is going to be located in Berlin, Germany, and neighboring suburban areas. The study center will be located at the Department of Psychology, MSB Medical School Berlin. The method center (i.e., external evaluation) will be located at the Institute for Medical Sociology and Rehabilitation Science, Charité – Universitätsmedizin Berlin.

### Participants, interventions, and outcomes

#### Study setting

The psychotherapy intervention will take place in psychotherapy practices or – in case of a participant’s impaired mobility or confinement to bed – at participants’ homes (i.e., in that case psychotherapists will be traveling to participants’ homes). The control group will receive treatment via telephone (psychosocial counseling) and postal service (self-help literature; audiobook or printed version).

#### Eligibility criteria

Participants will be included in the study if they [1] are 60 years and older (women/ men) [2]; are living at home (Berlin, Germany) [3]; have a long-term care grade, as assessed by the German compulsory state nursing care insurance (1 = little impairment to 5 = hardship case; see [29]) [4]; show clinically relevant depressive symptoms (major depression; adjustment disorder with depressive symptoms; dysthymia); and [5] are willing to participate in one of the two treatments. Exclusion criteria will be moderate to severe dementia as well as delirium, acute psychosis or other cognitive disorders, mania or hypomania or terminal stage of a disease. Further reasons for exclusion will be currently receiving psychotherapy, communication difficulties and visual or hearing impairments that would severely affect an individual’s capability to take part in the study. Reasons for participant exclusion will be recorded.

#### Interventions

Participants included in the study will be randomly assigned to one of two treatment groups (intervention condition versus active control condition). the intervention condition, outpatient short-term psychotherapy tailored to the specific needs of vulnerable older adults, will be offered by residential CBT psychotherapists with extensive geriatric and geropsychiatric experience as part of the regular healthcare service. After the taking of an anamnesis, a medical examination by a general practitioner or a medical specialist and test sessions, participants will be treated in up to 24 therapy sessions. Psychotherapeutic treatment, as described in the PSY-CARE manual, follows the regular CBT rationale, but is augmented by psychotherapeutic techniques of a) reminiscence, b) empowerment and c) inclusion of participants’ social systems, based on existing effective psychotherapeutic approaches for vulnerable older adults with depression (see above). Before participating in PSY-CARE, psychotherapists will be trained in the assessment of depression in vulnerable older adults and the application of the PSY-CARE Manual.

The active control condition will include individual telephone counselling carried out by project staff members as well as self-help literature for participants and their caregivers. The telephone counselling will be offered two times per participant and per caregiver by members of the project team (all trained certified psychotherapists). In addition, control group participants and their caregivers will receive a print or audio version of a self-help guide based on existing literature on depression in later life [e.g., [30]], which will include psychoeducation and self-help instructions. For participants in the control condition, regular psychotherapy will not be retained if desired.

Critical events for intervention or control participants will be recorded. In order to improve and monitor the adherence to intervention protocol, psychotherapists will be regularly supervised by PSY-CARE supervisors. The project team will stay in contact with participants via telephone or letters on a regular basis.

#### Outcomes

The primary outcome variable is the reduction of depressive symptoms of the participants assessed by the 12-item Geriatric Depression Scale (GDS [31, 32];) at baseline (T1), directly after the intervention (T2), and at follow-up after 3 months (T3) compared to baseline. Total scores range from 0 to 12, a score of 4 or more indicates the presence of clinically relevant depressive symptoms.

Secondary outcome variables are participants’ [1] quality of life measured by a single item from the World Health Organization Quality of Life in old age, i.e. WHOQOL-OLD [2, 33]; the diagnose of depressive symptoms (major depression; adjustment disorder with depressive symptoms; dysthymia; F32, F33, F34, F43), assessed by a German structured clinical interview for psychological diseases (Mini-DIPS [34];) as well as depressive symptoms (and comorbid anxiety) assessed with the Hospital Anxiety and Depression Scale (HADS [35];) [3] Activities of daily living and functioning measured using the Barthel-Index and the IADL-Scale [36, 37]; and [4] self-rated health measured by a single item asking “How would you estimate your health status in the last 4 weeks?” on a 6-point Likert scale from 1 = “very poor” to 6 = “excellent”. Treatment response (50% or greater reduction in depressive symptoms from baseline to follow up) and remission (defined as number of individuals who scoring below the cut-off of 10 points at the GDS at follow up) will be used as secondary outcomes. All secondary outcomes will be assessed at Baseline (T1), after the intervention (T2), as well as at follow-up after 3 months (T3).

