#### Sample size

For sample size estimation, a difference in depression (i.e., primary outcome) between intervention and control group at follow-up of medium effect size is considered as clinically relevant (Cohen’s d = 0.5), which also corresponds to finding from a recent meta-analysis [8]. The sample estimation (test family: t-test for independent samples) with Gpower 3.1 [38] yielded an estimated minimum sample size of the two groups of *n* = 51 at a Type I error rate of alpha = 0.05 and a statistical power of 1-beta = 0.80 individuals. If a dropout rate of 20% is taken into account [39], as was the case in comparable studies, the final rounded sample size per group is *n* = 65, or *N* = 130 persons in total. While 20% of drop out is common in psychotherapy trails for older adults, considering the vulnerability of our sample of vulnerable participants, we will be collecting further participants to guarantee sufficient statistical power at follow up.

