### Data collection, management and statistical analysis

Standardized assessments will be carried out at baseline, directly after the intervention and at a follow-up after 3 months. The quantitative assessment (Hypotheses 1 and 2) among participants will be carried out by two trained study nurses (clinical psychologists with advanced clinical training). The questionnaires will be conducted as computer assessed interviews using a secure laptop and will take up to a maximum of two hours per participant. Data collection will be monitored by the method center and later automatically transferred to SPSS v25 (IBM, Cary, Ind.). When selecting the measuring instruments, attention was paid to the objectivity, reliability, and validity of the assessments.

Psychotherapists will also complete questionnaires in paper-pencil format and later transferred to a SPSS v25 data mask. Missing data will be handled using multiple imputation. Furthermore, qualitative data will be collected from psychotherapists, gatekeepers and older participants. Data will be stored and analyzed at the method center. Only the evaluation team will have access to the data, as defined in the data protection concept as part of the ethics approval.

The evaluation based on participant data will be carried out by means of multivariate longitudinal methods (random effects models). Both intention-to-treat analyzes and completers analyzes will be carried out. A post hoc effectiveness analysis of three potentially moderating characteristics of those in need of care will be considered: (a) degree of cognitive impairment, (b) drug use, and (c) late-onset versus early onset depression. In addition to effect sizes, remission and response rates (Reliable Change Index; RCI) will be determined.

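### T2 and T3 are anchored to the end of the intervention, with no fixed time since randomisation and no stated rule for when control participants are assessed

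*Protocol article*

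**What the plan says.** The protocol article gives the visit timing in four places, each time by reference to an event:

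- Outcomes: the GDS is taken "at baseline (T1), directly after the intervention (T2), and at follow-up after 3 months (T3) compared to baseline".
- Data collection, management and statistical analysis: "Standardized assessments will be carried out at baseline, directly after the intervention and at a follow-up after 3 months".
- Abstract, Methods: questionnaires are "provided at baseline, after the end of the intervention and after three months".
- Table 1, abbreviations: T2 is "Time point 2, after the intervention".

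The two arms differ greatly in content. Table 1, footnote a, gives the psychotherapy arm as "Three probationary sessions and up to 24 therapy sessions". For control, the Interventions section says "The telephone counselling will be offered two times per participant and per caregiver by members of the project team", and adds a self-help guide in print or audio. Neither arm has a stated duration in weeks, and no interval between sessions or calls is given.

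The Sample size section places the design contrast at follow-up: a difference "between intervention and control group at follow-up of medium effect size is considered as clinically relevant", with d = 0.5.

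**The concern.** In a randomised comparison, both arms should be measured at the same time since randomisation, so that whatever happens with time alone cancels out. A visit fixed by the end of treatment does this only if treatment lasts equally long in both arms. Here one arm has up to 27 sessions and the other has a few telephone calls.

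Three things are at stake.

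- **Confounding of arm with time.** Participants enter because they have clinically relevant symptoms, so some change without treatment is to be expected. If symptoms improve spontaneously, a later psychotherapy visit favours psychotherapy on the GDS. For quality of life, daily activities and functioning, the Objectives section assumes that controls decline. A control visit held early would miss part of that decline and work against psychotherapy.
- **A visit date set after randomisation.** The number of therapy sessions has an upper limit only. A participant who stops early has either an early T2 or no clear T2. That sits badly with the planned intention-to-treat analysis and an allowance of 20% dropout.
- **Carry-over to T3.** If T3 is three months after T2, any gap between the arms at T2 is passed on to follow-up, where the sample size places the primary contrast.

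**Working it through.** **1. What the documents fix.**

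| Item | Psychotherapy | Control |
|---|---|---|
| Content | 3 + up to 24 = up to 27 sessions | 2 calls to the participant + 2 to the caregiver = up to 4 calls, plus self-help guide |
| Interval between contacts | not given | not given |
| Duration in weeks | not given | not given |
| T2 | after the intervention | not separately stated |
| T3 | after 3 months | not separately stated |

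**2. Two readings of the timing rule.**

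- *The intervention is what each participant was allocated to.* The Objectives section supports this by describing the counselling as an alternative intervention. T2 then follows each arm's last contact, and the arms are assessed at different times.
- *The intervention is psychotherapy only.* Trial design and Interventions support this, since they call one arm the intervention condition and the other the active control condition. Control T2 then has no definition. As therapy length varies by participant, there is no single period to match it to unless a rule is given.

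Neither reading yields a common, fixed assessment time.

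**3. The yardstick.** The plan's effect is 0.5 SD "at a Type I error rate of alpha = 0.05 and a statistical power of 1-beta = 0.80". An exact independent-samples t-test gives 50.15, so 51 per group (power 0.806), with a one-sided alpha of 0.05. Then 51 / 0.8 = 63.75, so 64, which the plan rounds to 65. A two-sided test would need 63.77, so 64 per group before dropout. Sidedness is a separate matter. The check is used here only to confirm 0.5 SD as the design effect.

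**4. Illustration under the first reading.** All inputs in this step except the 27 sessions are assumptions: control calls finish in 2 to 8 weeks, a month is 4.345 weeks, and a common linear drift of 0.01 to 0.05 SD per month applies in both arms.

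Gap in weeks = 27 × weeks per session − weeks to end of control calls.

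Shift in SD = drift per month × gap / 4.345.

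| Assumed session interval | Psychotherapy ends | Gap | Smallest shift | Largest shift |
|---|---|---|---|---|
| Half a week | 13.5 weeks | 5.5 to 11.5 weeks | 0.01 × 5.5 / 4.345 = 0.01 SD | 0.05 × 11.5 / 4.345 = 0.13 SD |
| One week | 27 weeks | 19 to 25 weeks | 0.01 × 19 / 4.345 = 0.04 SD | 0.05 × 25 / 4.345 = 0.29 SD |
| Two weeks | 54 weeks | 46 to 52 weeks | 0.01 × 46 / 4.345 = 0.11 SD | 0.05 × 52 / 4.345 = 0.60 SD |

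For weekly sessions the shift is 0.044 / 0.5 = 9% to 0.288 / 0.5 = 58% of the planned effect. With 24 sessions instead of 27, the weekly gap is 24 − 8 = 16 to 24 − 2 = 22 weeks.

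**5. Can the model repair it?** The article names random effects models and does not say how time enters. Take the weekly case, with T3 13 weeks (3 × 4.345) after T2. Controls would be seen at 2 to 8 and 15 to 21 weeks, and a participant completing 27 sessions at about 27 and 40 weeks. On those assumptions the post-baseline times do not overlap. A model using actual time would then compare the arms by extrapolation.

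**The case against.** The strongest reply is that a reader might infer that T2 and T3 are timed from the end of each arm's own treatment, and no sentence says so. The wording is singular throughout, and the arm labels reserve the word intervention for psychotherapy. The self-help guide has no stated end, so control treatment has no obvious last day. Control visits may well be matched to the psychotherapy period. The bodies of Table 1 and Fig. 1 are not shown in the copy reviewed and could carry week numbers or a matching rule. Visit windows are also often left to the full protocol. This stands: the own-arm reading is an inference, and unequal timing is a consequence of a literal reading, not a documented fact.

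It does not dispose of the point. The article does define T2, in four places, and each definition depends on an event after randomisation whose length varies. That is a rule badly fixed, not a detail left out. If the own-arm reading is wrong, control T2 has no rule in the visible text.

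A second reply concerns size. A reader might infer from the two-week row of the table that the bias could exceed the planned effect. The documents do not support that: they give neither gap nor drift, and regression to the mean appears largely at the first re-measurement and does not build up month by month. A linear drift is a simplification.

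A reader might also infer that arm-specific visit dates reveal allocation to the interviewers. The article promises blinding of staff who evaluate the results and does not expressly say that the interviewers are blinded. The inference also needs the own-arm reading, so it is not part of this point.

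**Conclusion.** The point holds in this form: the primary outcome visits are tied to the end of the intervention, no time since randomisation is fixed, and the visible text has no rule for the control arm. Followed literally, the plan compares the arms at different times and lets a variable post-randomisation event set the endpoint visit. Otherwise control T2 is undefined. Both outcomes affect the validity of the primary comparison.

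The size is not known. The figure of about 0.04 to 0.29 SD, against 0.5 SD, rests on assumed weekly sessions, control calls ending within 2 to 8 weeks, and linear drift of 0.01 to 0.05 SD per month. It shows that the problem could matter, not that it is that large. The direction differs by outcome: towards psychotherapy on the GDS if symptoms improve spontaneously, and against it on secondary outcomes that decline.

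**What to change.** Define T2 and T3 in both arms at the same time from randomisation, with the same windows: T2 at the expected length of the psychotherapy course, T3 three months later. Assess every participant at those times whether or not treatment is complete. If control visits are in fact already matched to the psychotherapy period, state the matching rule in the text.

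Enrolment began on 25/02/2019, so visits already held cannot be moved. For those participants, report time since randomisation by arm and visit, and use actual assessment time in the random effects model. This reduces the confounding but does not remove it if the visit times of the arms barely overlap, and the report should say so.

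The cost is an amendment to the visit definition and the rescheduling of control visits still to come. No visits are added. The downside is that some psychotherapy participants will still be in therapy at T2, so for them T2 no longer measures the end of treatment.
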